#### Quality of Life (QoL)

QoL will be assessed using FACT-HN questionnaire at baseline, once during treatment at the 4^th^ or 5^th^ fraction, at 6 weeks, and then at 3, 6, 12 months follow-up.

### Application of RECIST 1.1 for SBRT outcomes assessment

The RECIST 1.1 criteria were developed using data from cytotoxic drug trials. Radiotherapy is excluded in the majority of studies using RECIST and therefore must be clearly defined for use in the setting of this SBRT study. In this radiation study the ‘target lesions’ must be pathologically enlarged and measurable as per the RECIST 1.1 criteria: primary tumour ≥ 10 mm measured in the longest axis, and lymph nodes ≥ 15 mm in the shortest axis. CT imaging is the preferred method of measurement in all cases; exceptions will be allowed only if the patient is unable to have CT imaging of the target lesion and also has a superficial skin tumour that can be reproducibly measured using calipers. Lymph nodes ≥ 10 mm and < 15 mm are considered non-target, non-measurable lesions and will be documented but not considered in the radiation response assessment. A maximum of 4 target lesions will be measured at baseline: up to 2 primary tumour targets and the 2 largest target lymph nodes. A sum of diameters of the target lesions will be calculated based on the baseline CT scan and all subsequent CT scans to quantify response.

The baseline CT scan will be done no more than 4 weeks prior to the start of SBRT; CT simulation scan measurements will be used if the diagnostic scan is > 4 weeks prior to SBRT.

Complete response (CR) is defined as disappearance of the target lesion for primary tumours AND reduction of target lymph nodes to < 10 mm in the shortest axis for lymph node metastasis. Partial response (PR) is defined as at least 30% decrease in the sum of diameters of the target lesions [20, 22]. Local progression of disease (PD) in-field is defined as ≥ 20% increase in the sum of diameters of the target lesions measured at baseline or smallest sum of diameters measured in follow-up. Stable disease (SD) is defined as neither sufficient shrinkage from baseline or sufficient increase from smallest sum of diameters to qualify as CR, PR, or PD. New pathologically enlarged lesions outside of the target lesions and/or new distant metastases will be documented and defined as progression of disease outside the high dose radiation field – and will be further sub-classified as nodal or distant. Response assessment must be a minimum of 6 weeks from the start of SBRT to qualify as CR, PR or SD. All eligible patients will have follow-up imaging scheduled 10–12 weeks following the completion of treatment which will be used to assess tumour response. No additional confirmatory imaging is required on the study; if any additional diagnostic imaging is performed by the treating physicians then it will be included in the assessment of response / progression status. The best overall response across all time points will be used.

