#### Target delineation and treatment of the primary tumour

The prescription dose GTV45 volume will be contoured on neck / soft tissue windows by the treating radiation oncologist to include all tumour regions and abnormal tissue on CT and MRI simulation images. No high dose CTV expansion will be used. A 5 mm expansion from GTV45 will be used to determine the high dose PTV45.

A microscopic dose CTV volume of 27 Gy/5 fractions will be contoured for the primary tumour. CTV27 will consist of the GTV with an expansion of 10 mm to encompass microscopic disease excluding air and anatomic boundaries such as bone and adjacent intact muscle planes. An additional 5 mm expansion will be used to determine the microscopic dose PTV27.

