#### Local Control (LC)

Defined as the absence of local progression of disease of the target lesions during the study period. Operationally, this is the time from enrollment registration to progression of the treated lesion(s). Subjects without local recurrence will be censored at the earliest date of last follow-up or death. Determination of local recurrence will be based on RECIST criteria 1.1 (see Sect. 11.3 below) and assessed on MRI or CT scan imaging at 12 weeks and any additional imaging/clinical assessments performed during the study.

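### A new non-nodal lesion at the primary site, inside or at the edge of PTV45, is labelled out-of-field by definition and cannot count as a local failure

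*Protocol article*

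**What the plan says.** Three parts of the protocol article bear on this.

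- **Application of RECIST 1.1 for SBRT outcomes assessment.** Local in-field progression is a rise of at least 20%, expressed as an "increase in the sum of diameters of the target lesions measured at baseline or smallest sum of diameters measured in follow-up". For anything else that appears, the rule refers to the high dose field: "New pathologically enlarged lesions outside of the target lesions and/or new distant metastases will be documented and defined as progression of disease outside" it. Such lesions "will be further sub-classified as nodal or distant".
- **Local Control (LC).** The endpoint is the "absence of local progression of disease of the target lesions during the study period". The next sentence makes it operational as time from registration to progression of the treated lesion or lesions, which is a wider term. The section then adds: "Determination of local recurrence will be based on RECIST criteria 1.1".
- **Target delineation and treatment of the primary tumour.** The high dose PTV45 is GTV45 plus 5 mm. For the microscopic dose, "CTV27 will consist of the GTV with an expansion of 10 mm to encompass microscopic disease", and a further 5 mm gives PTV27.

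Local control, locoregional control and progression free survival are all named under Secondary objectives. The article defines local control but not locoregional control.

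**The concern.** The new-lesion rule treats not being a target lesion as equivalent to lying outside the high dose field. The planning volumes show that these differ, because the high dose field includes a rim of tissue beyond the visible tumour. A separate nodule arising in that rim is in-field by geometry and out-of-field by definition. It must then be sorted as nodal or distant, and it is neither.

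The plan uses no high dose CTV expansion, so failure at the edge of the treated primary is an informative pattern for this trial. If such events are not local failures, estimated local control can only rise: in a crude proportion they leave the failure count, and in a time-to-event analysis they are censored instead of counted.

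**Working it through.** **1. The plan's own figures.** The documents give no rate, sample size or power for local or locoregional control, so there is no stated figure to reproduce for this endpoint. The only design figures belong to the primary outcome (Simon design, 6/11 then 26/38). An exact two-stage binomial calculation gives α = 0.0970, β = 0.0958 and a stage I stopping probability of 0.4672, against the stated 0.097, 0.096 and 0.467. They agree, and the new-lesion rule does not enter them.

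**2. Where each kind of recurrence goes under the text.**

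- Regrowth of a target lesion, including after complete response: counted as local progression, because the reference is the smallest sum on follow-up.
- New separate non-nodal lesion inside PTV45 or across its edge: labelled outside the high dose field, which contradicts the PTV45 definition. No sub-class fits, and it is not a local failure under the target-lesion wording.
- New separate non-nodal lesion between PTV45 and PTV27: correctly described as outside the high dose field, but again no sub-class fits.
- New regional node: nodal.
- New distant metastasis: distant.

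**3. Target versus treated lesions.** The nodal delineation section treats nodes with a short axis of 1 cm or more. The RECIST section makes nodes of 10 to under 15 mm non-target and leaves them out of the response assessment. It also caps target lesions at four. Regrowth of such a node is progression of a treated lesion but not of a target lesion, so the two sentences defining local control can give different answers for the same patient.

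**4. Geometry (assumption: spherical GTV, no trimming at anatomical boundaries).** For a 3 cm GTV the radii of GTV, PTV45 and PTV27 are 15, 20 and 30 mm.

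- Share of PTV45 outside the GTV: 1 − (15/20)³ = 57.8%. For a 2 cm GTV it is 1 − (10/15)³ = 70.4%; for 4 cm, 1 − (20/25)³ = 48.8%.
- Rim between GTV and PTV45 as a share of PTV27: (8000 − 3375)/27000 = 17.1%.
- Share of PTV27 beyond PTV45: 1 − (20/30)³ = 70.4%.

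These are volumes, not probabilities of recurrence. They show only that the rim is a real part of the high dose field.

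**5. Effect on local control (assumed counts, n = 38, the planned maximum).** Each misfiled failure in a patient with no other local failure adds 1/38 = 2.6 points to the crude proportion, whatever the number of recorded failures. One to four misfiled failures add 2.6 to 10.5 points. If 8 failures are recorded:

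- reported: 30/38 = 78.9% (exact 95% CI 62.7 to 90.4)
- with 2 misfiled, correct value: 28/38 = 73.7% (56.9 to 86.6)
- with 4 misfiled, correct value: 26/38 = 68.4% (51.3 to 82.5)

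With 4 recorded failures, four misfiled would move 34/38 = 89.5% to 30/38 = 78.9%. With 13 recorded, 25/38 = 65.8% would become 21/38 = 55.3%.

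**The case against.** The strongest reply is that this is a narrow gap. Most in-field recurrence will be regrowth of the treated tumour, which is counted. The operational sentence for local control speaks of treated lesions and allows any additional imaging or clinical assessment. Under Cancer recurrence and other cancer events, the site of first recurrence is recorded, so the failure pattern could be recovered. The rim is 5 mm thick, so a new lesion meeting the 10 mm size threshold for target lesions could not lie wholly inside it. A new lesion is still called progression, so progression free survival need not miss it. Local control carries no hypothesis or decision rule, and the intervals above are wide and overlap.

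Much of this stands and limits the point. It does not remove it. A lesion straddling the rim is not outside the high dose field, yet the rule says that it is. Recording the site does not change what the endpoint definition counts. The broader treated-lesion wording is not reconciled with the target-lesion wording beside it. Nor is this a detail left to a fuller document: the RECIST section says that the criteria must be clearly defined for this setting and then states the rule.

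**Conclusion.** The point holds for a discrete new non-nodal lesion at the primary site, inside or at the edge of PTV45. The text mislabels it, gives it no sub-class and, on the target-lesion wording, does not count it as local failure. The bias in local control, a stated secondary endpoint, can only be upward. The documents do not give its size; the illustrations rest on assumed counts and a crude proportion.

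Three stronger readings are not supported:

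- A reader might infer that an in-field recurrence is never a local failure. Regrowth of a target lesion is one.
- A reader might infer that most of the treated volume is mislabelled. Under the 3 cm assumption, about 70% of PTV27 lies beyond PTV45, where the out-of-field label is correct. Whether marginal lesions count as local failure is a convention that the documents do not settle.
- A reader might infer that locoregional control is overstated. The article does not define that endpoint and new nodal disease has its own class, so an effect is possible but not shown.

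**What to change.** In the RECIST section, replace the new-lesion rule with a classification by position on the stored treatment plan: inside PTV45; between PTV45 and PTV27 (marginal); regional outside PTV27; distant. Say how a lesion straddling a boundary is assigned.

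Count new lesions inside PTV45 as local failure. Report marginal primary-site lesions as their own category, with a statement fixed in advance of whether they count as local failure.

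In the Local Control section, use one term that covers all treated lesions, and make the RECIST section's in-field progression rule agree with it.

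The cost is protocol and case report form wording, plus a comparison of each failure scan with the stored plan. No new imaging is needed. Reported local control may be slightly less favourable.

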## Statistical considerations

### Sample size calculation and assumptions

Up to a total of 38 patients will participate in this single institution, single arm, phase 2 study. Based on prior research, the response rate for patients treated using the’0–7-21’ regimen was 82%, however, 6-month progression-free survival was only 39%. Given the expected relative minimal toxicity and ease of treatment using this regimen, a similar response rate of around 80% would be of considerable interest, while a response rate of 60% or lower would indicate that there would not be any interest in studying this regimen further. Hence, for sample size calculations, it will be assumed that H0: *p* = 60% versus HA: *p* = 80%, with α = 0.10 and β = 0.10. Using the Simon optimal two-stage design, 11 patients will be recruited in the first stage. If 6 or less patients have a response, the study will be stopped at the end of stage I, however, if 7 or more patients have a response the study will continue to stage II, in which an additional 27 patients (for a total of 38) will be recruited. At the end of stage II, if 26 or less patients have a response, then H0 will be accepted and the treatment regimen deemed not worthy of further study, however, if 27 or more patients have a response, the treatment regimen will be recommended for further study in phase III. The true α = 0.097 and β = 0.096 for this design, with a probability of termination at the end of stage I of 0.467.

### Statistical analysis

Tumour response and control will be reported based on all available clinical/imaging measurements and classified using the RECIST criteria. Adverse events will be summarized using the NCI-CTCAE. The number of patients with grade ≥ 2 toxicity will be reported. Any grade 4–5 toxicity or adverse event on the study will be reported. Baseline demographics, tumour characteristics and reason for no surgical management will be reported with descriptive statistics. The baseline Charlson Comorbidities Index, VES13 and G8 scores will be summarized to assess the study population for vulnerability/frailty. Quality of life and symptom scores will be assessed to identify the severity and duration of changes to these scores during and after SBRT. Exact confidence intervals will be constructed for outcomes of interest and statistical significance will be defined as a two-sided α ≤ 0.05 for all analyses other than the primary outcome. No interpolation will occur for any missing information.

All patients who receive at least one protocol defined treatment will be included in all analyses. Any patient registered to this study who does not receive protocol defined treatment will be described, including reasons for not receiving treatment, but will not be included in further analyses.

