## Pretreatment evaluation and subject enrollment

Following the multi-disciplinary consultation including a head and neck surgeon and radiation oncologist, patients who meet the inclusion criteria will be screened and approached for eligibility assessment and potential study enrollment. Written informed consent is obtained for all eligible patients prior to commencing any study related procedures.

All potentially eligible and consenting patients who do not meet the exclusion criteria will have a CT simulation of head and neck region. Based on our experience in the head and neck clinic, less than 10% of patients in this population will be unable to tolerate the CT with head and neck immobilization. Patients who cannot tolerate the simulation procedure with immobilization will be treated off study.

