## Safety monitoring plan

Patients treated with HN SBRT on this study are anticipated to have significant frailty and co-morbidities that preclude surgery, conventional radiotherapy and systemic therapy. Studies involving a similar patient population at JCC and other centres reported median survival between 5–6 months and deem the treatment intent to be palliative [9-11]. Head and Neck cancer patients in Ontario are known to have a high rate of emergency room visits and hospitalizations [3]. Therefore, it is likely and expected that some patients may be admitted to hospital or die during the duration of the study; this may be caused by complications due to the tumour and associated treatments or for reasons unrelated to the cancer diagnosis.

A data safety monitoring committee (DSMC) consisting of at least two radiation oncologists who are not co-investigators in the study will review all grade 4 or 5 (severe) adverse events. Any severe adverse events will be classified as definitely related, possibly related or not related to the study intervention. Toxicity will be reviewed by the DSMC on a q6 monthly basis or more frequently if unexpected toxicity is observed. If grade 5 toxicity is observed in more than 10% of patients, the protocol will be amended to a lower radiation dose (40 Gy) for REB review, or the study may be closed.

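### The 7/11 and 27/38 cut-offs are set on patients recruited but applied to patients treated, so the stated power of about 90% is not assured if any registered patient goes untreated

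*Protocol article*

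**What the plan says.** The section on sample size tests a 60% response rate against 80%. It regards 60% or less as of no interest ("a response rate of 60% or lower would indicate that there would not be any interest in studying this regimen further") and 80% as worth pursuing ("a similar response rate of around 80% would be of considerable interest"), "with α = 0.10 and β = 0.10". The design is a Simon optimal two-stage design. Eleven patients are recruited first, and the trial continues with 7 or more responses. Then "an additional 27 patients (for a total of 38) will be recruited", and 27 or more responses lead to a recommendation for phase III. Participation is limited to 38. The section reports a true alpha of 0.097, a true beta of 0.096 and a 0.467 probability of stopping after stage I.

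The section on statistical analysis defines who is analysed: "All patients who receive at least one protocol defined treatment will be included in all analyses". A registered patient who receives no protocol treatment is described but excluded from further analysis. On missing data it says "No interpolation will occur for any missing information".

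Two other places bear on the counts. Under pretreatment evaluation, consent comes before any study procedure, fewer than 10% are expected not to tolerate the planning CT, and "Patients who cannot tolerate the simulation procedure with immobilization will be treated off study". The safety monitoring plan notes that studies in similar patients "reported median survival between 5–6 months" and expects some deaths on study.

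**The concern.** A Simon design gives its stated error rates only when the responses are counted among exactly the planned numbers. Here one section counts patients recruited and the other counts patients treated, and the article itself provides for registered patients who are never treated. Followed literally, such a patient uses one of the 38 places and then leaves the denominator, while the requirement of 27 responses stays. The bar rises from 27/38 (71%) to 27/36 (75%) with two such patients. The trial could then judge the regimen not worth further study because of patients who never received it.

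There is a second, conditional question. Treated patients stay in the analysis even if they die or decline before a response can be assessed. Such a patient cannot add to the 27. Whether this costs power depends on whether the 80% already allows for it, and the article does not say.

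**Working it through.** **Inputs.** From the sample size section: null rate 0.60, alternative 0.80, stage I n1 = 11 (continue at 7 or more), total N = 38 (success at 27 or more).

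**Formula.** The probability of success at true rate p is the sum over x = 7 to n1 of P(Bin(n1, p) = x) × P(Bin(N − n1, p) ≥ 27 − x).

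**Reproducing the stated design (11/38).**
- p = 0.60: 0.0970, the stated alpha of 0.097.
- p = 0.80: 0.9042, so beta is 0.0958, the stated 0.096.
- P(Bin(11, 0.60) ≤ 6) = 0.4672, the stated 0.467.

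The published figures are correct for exactly 11 and 38.

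**Untreated registrants not replaced, cut-offs unchanged.** Stage I is kept at 11, so all losses fall in stage II. Ten per cent of 38 is 3.8, so the article's bound of fewer than 10% means at most 3 lost, that is, at least 35 treated.

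| Treated (stage I / total) | Alpha (p = 0.60) | Power (p = 0.80) |
|---|---|---|
| 11 / 38 | 0.097 | 0.904 |
| 11 / 37 | 0.066 | 0.869 |
| 11 / 36 | 0.042 | 0.814 |
| 11 / 35 | 0.025 | 0.734 |

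A single untreated registrant is enough to take power below 0.90.

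**Re-derived final cut-off, 36 treated.** Keeping 7 or more of 11 and requiring 26 or more of 36 gives alpha 0.082 and power 0.883. So 26/36 meets the 0.10 error limit, yet the rule as written calls it a failure. The cut-off does not simply drop by one with every loss: 26 or more of 37 gives alpha 0.117, above 0.10, so 27 must stay at 37 treated.

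**Treated but unassessed patients (conditional).** Suppose 80% is the rate among assessed patients only, and a fraction d of treated patients has no qualifying assessment and counts as non-response. The effective rate is 0.80 × (1 − d). The article gives no value for d, so these are assumptions:
- d = 2%: rate 0.784, power 0.86.
- d = 5%: rate 0.760, power 0.77.
- d = 10%: rate 0.720, power 0.58.

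If 80% is instead the rate over all treated patients, and 11 and 38 are treated, power stays at 0.904.

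**The case against.** The strongest reply is that nothing stated is miscalculated: beta 0.096 is right for the design described, and replacement rules are often left to the full protocol. Patients who fail simulation are treated off study, and inability to lie flat for planning is an exclusion, so they may be screening failures who are never registered. Keeping all treated patients is also the usual conservative convention in a single-arm response trial.

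Much of this stands. A reader might infer that the trial will not have 90% power. The article does not support that, because the loss depends on untreated patients being registered and not replaced. A reader might also take 34 treated patients (power about 0.61 with 10 in stage I), but that is a loss of 4 of 38, or 10.5%, outside the article's own bound.

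A third tempting inference is that early deaths must destroy the power, since median survival is 5 to 6 months and the one scheduled scan comes 10–12 weeks after treatment. This is not established either. Patients with a life expectancy of 3 months or less are excluded. A response can qualify from 6 weeks after the start of SBRT, and additional imaging counts. Tumour dimensions are also recorded at the 6-week visit, although calipers replace CT only for superficial skin tumours in patients unable to have CT. Finally, the 80% is anchored on patients treated with an earlier regimen and may already include early failures. Its basis is unclear: the Background describes that 82% as temporary symptom relief, whereas the sample size section calls it a response rate.

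What the reply does not remove is the mismatch. The article states both counting rules, a cap of 38 and fixed cut-offs, and it explicitly foresees registered, untreated patients. Together these rules can produce a worse decision than the one designed.

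**Conclusion.** The point holds as a mismatch between two stated rules. The cut-offs and error rates are valid only for response denominators of 11 and 38, and the text does not secure those numbers. If one to three registered patients go untreated in stage II, are not replaced and the cut-offs stay, power is between 0.869 and 0.734 instead of 0.904. Type I error falls at the same time, so the risk is a false negative and not a false claim of activity.

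The part about unassessed treated patients is a request for clarification. It costs power only if 80% refers to assessed patients, and its size rests on an assumed loss rate.

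**What to change.** In the sample size section, define 11 and 38 as patients who have received at least one fraction, and say that untreated registrants count towards neither stage. This restores alpha 0.097 and power 0.904. It costs at most a few extra consents, and no more patients are treated than planned.

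If 38 registrations is a hard cap, state that the final cut-off will be re-derived for the number treated, and restate the power. With 36 treated that is 26 or more after 7 or more of 11 (alpha 0.082, power 0.883). The cost is a stated power slightly below 90%.

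In the statistical analysis section, add that a treated patient without a qualifying assessment is a non-responder at both the stage I and the final decision, and that the 80% is a rate over all treated patients. If 80% is meant among assessed patients only, restate power over an assumed loss range, such as the 2%, 5% and 10% worked above.
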